# Social phobia and evasiveness: trial protocol for a randomized controlled feasibility and superiority trial of the effect of Modified Collaborative Assessment vs. standard assessment on patients’ readiness for psychotherapy (CO-ASSM-RCT)

**DOI:** 10.1186/s40814-023-01332-z

**Published:** 2023-06-20

**Keywords:** Assessment, Personality disorders, Social phobia, Psychotherapy, Evasiveness, Collaborative assessment, Therapeutic assessment

## Abstract

**Background:**

Evasive personality disorder (AvPD) and social phobia (SP) have substantial costs for patients and their families and great economic costs to the society. While psychotherapy can be an efficacious treatment, many patients drop out during treatment. Increased knowledge on how to decrease dropout from psychotherapy is warranted, including how to increase a patient’s readiness for psychotherapy.

**Methods:**

We describe a randomized controlled feasibility and superiority trial of 42 individuals with a clinical diagnosis of either SP or AvPD, who are to initiate psychotherapeutic treatment in Danish outpatient mental health services. They will be randomized in a 1:1 ratio to either assessment-as-usual and receive no further assessment or to a Modified Collaborative Assessment (MCA) provided as a pre-treatment intervention before psychotherapy initiation. MCA will include a battery of psychological tests designed to thoroughly assess the patients’ psychopathology. The tests are administered in collaboration with the patient, including detailed oral and written feedback. We hypothesize that the intervention is feasible regarding patient’s acceptance and adherence. We further hypothesize that patients randomized to MCA will reach higher levels of readiness for psychotherapy as assessed with the University of Rhode Island Change Assessment Scale (URICA).

**Discussion:**

This protocol assesses the feasibility, efficacy, acceptability, and safety of an intervention aimed at changing the readiness for participation in psychotherapy of patients with SP and AvPD. Results from this feasibility study could guide the development of future large-scale trials of MCA and procedures for MCA treatment fidelity assessment.

**Trial registration:**

NCT2021001.

## Background

### Introduction and rationale

Anxiety disorders represent an important public health concern in the Western world [1, 2]. Estimates from a large European epidemiological survey suggest that 14% of the European population will meet the criteria for an anxiety disorder within their lifetime [3]. These disorders are often associated with a chronic, debilitating course for the affected individual as well as high socio-economic costs [4–6]. Anxiety disorders are among the leading causes of the global disease burden and the annual costs in Europe alone reached 74 billion Euros in 2010 [7, 8]. Continuous efforts to improve treatment programs for anxiety pathology are imperative.

Social phobia (SP) is the most common among the anxiety disorders. The fear of being observed or negatively evaluated by other people is a prominent characteristic of individuals with social phobia. This fear leads the individual to avoid performance or social situations (e.g., speaking or eating in front of others, making acquaintances, and meeting authorities), or enter such situations with substantial discomfort [9]. This evasiveness severely impacts the social functioning and quality of life of affected individuals [10, 11].

Similarly, avoidant personality disorder (AvPD) is characterized by a pervasive pattern of social inhibition, feelings of inadequacy, and hypersensitivity to negative evaluation, which result in marked evasiveness and avoidance of social interactions. AvPD patients perceive themselves as unwanted and isolated from others [9]. The Diagnostic and Statistical Manual of Mental Disorders, fifth edition (DSM-5) [12], recognizes a considerable overlap between AvPD and SP. Although the relationship between the disorders is a matter of debate [13], the dominant conceptualization is that the two disorders represent a spectrum, differing from each other only in severity (the severity continuum hypothesis [14]). In the upcoming revision of the International Classification of Diseases, tenth edition (ICD-10), AvPD will be removed as an independent diagnosis [15], which further supports the severity continuum hypothesis. Similar to the anxiety disorders, AvPD is associated with profound impairment in daily life for the affected individual, as well as high socio-economic costs [16]. Hence, the present study protocol relevantly focuses on SP and social evasiveness.

Danish outpatient mental health services provide time-restricted, standardized, interdisciplinary treatment programs for social phobia and AvPD. Following national clinical practice guidelines, the treatment programs offer evidence-based cognitive-behavioral therapy for social phobia and mentalization-based therapy for AvPD.

The content and format in the standardized treatment programs for moderate-severe SP and AvPD are regulated in accordance with the Danish Health Authority guidelines. The treatment program for SP consists of diagnostic assessment (1–3 consultations), medical consultations (1–2 consultation), and group therapy with two therapists (14 sessions (120 min)), relatives’ support (1 session), and network consultation (1 session) [17]. Correspondingly, the standardized outpatient treatment program for AvPD includes up to 78 h of clinician time consisting of clinical assessment (2 h), medical consultations (1–2 consultations), group therapy with two therapists (30 sessions (120 min)), and network consultation (1–2 sessions) [18].

However, despite a solid evidence base for the efficacy of cognitive-behavioral therapy for social phobia, recent meta-analytic data suggest that only 45% of patients suffering from social phobia remit from their principal diagnosis after treatment and patients with social phobia have a worse outcome than patients with other anxiety disorders [19]. The evidence-based psychological treatment for avoidant personality is limited in terms of number and quality of studies and the remission rates vary substantially from 40 to 80% [20].

Data from a recently finalized multicenter randomized controlled trial [21] investigating the relative efficacy of group diagnosis-specific versus transdiagnostic cognitive-behavioral therapy for anxiety disorders or depression supports the meta-analytic findings on social phobia. In this trial, 291 patients with anxiety disorders or depression received standardized treatment programs from three Danish mental health services, and the results suggested that only half of the patients no longer met diagnostic criteria for their principal diagnosis by the end of treatment [22]. No data exists on the efficacy of the standardized programs for AvPD.

### Modified collaborative assessment

Psychiatric assessment usually aims to establish a diagnosis and plan the treatment, but it is not considered part of the treatment proper. We wish to alter this perspective by the introduction and exploration of a modification of Collaborative Assessment that we have chosen to name Modified Collaborative Assessment (MCA).

MCA takes off from Collaborative Assessment and Therapeutic Assessment (C/TA) [23–25]. These terms are used to describe a family of semi-structured, brief therapeutic interventions, in which a therapist administers a large battery of standardized diagnostic and psychological tests in collaboration with a patient and delivers feedback in a manner that is useful and enriching—and therefore therapeutic—for the patient.

C/TA has been explored in several controlled trials with adults and has been shown to increase a range of process variables related to therapy outcomes. This includes self-esteem [26–29], compliance with treatment recommendations [30], therapeutic alliance with subsequent therapist [31, 32], and satisfaction with treatment [33], as well as decreased anxiety symptoms [34, 35] and levels of self-criticism [34]. In addition, Poston and Hanson [36] published a meta-analysis on 17 published C/TA studies, which found favorable effects of this intervention in terms of overall effectiveness when compared to assessment as usual.

We wish to apply a modification of C/TA, where the intervention is shorter, is slightly more structured, and requires less psychiatric expertise (i.e., it can be carried out by trainee doctors and psychologists), which we therefore expect to be more feasible in the trial as well as in later implementation.

Like C/TA, MCA will include the administration of standardized diagnostic instruments, but in contrast to C/TA, we will only include a smaller selection of tests in order to secure feasibility. The battery of tests will be specifically designed to gather information on psychopathology which a brief clinical interview might not detect, such as symptoms of previously undetected developmental disorders or incipient psychosis. We have compiled a battery of tests with this focus because we find it most suitable for application in the Mental Health Service. The present study is further designed to establish diagnosis adhering to the current diagnostic systems (ICD-10 and DSM-5), but we expect it would also be applicable if the Mental Health Service introduced the dimensional [37, 38] model of psychopathology, since the current MCA also includes a thorough personality assessment according to the DSM-5 alternative model of personality pathology.

MCA emphasizes respect for the patients as “experts on themselves.” The assessor will, in collaboration with the patient, formulate a list of therapeutic questions which the patient would like to “ask the psychological tests.” This will help guide the patient and assessor’s collaborative quest to learn more about the patient’s problems and personal resources. The results of the assessment and the answers to the therapeutic questions will be communicated, respectfully, to the patient both orally and in writing. It will further be communicated to the patient’s future therapist in writing. In this manner, it should be possible to formulate personally relevant problems for later psychotherapy. The MCA assessor recognizes that diagnostic assessment is an interpersonal event and that the relationship between assessor and patient is paramount both in relation to the validity of the result and the patient’s further treatment [25].

In short, MCA is a brief, individualized, and person-centered assessment of psychopathology, where assessment, psychotherapy, and psychoeducation are integrated into a novel intervention, all carried out in collaboration with the patient.

### Readiness for psychotherapy

The fundamental role of patients’ readiness for psychotherapy change (or client motivation) in the outcome of therapy is widely recognized [39]. The overall concept refers to the intentional aspect of change, the internal drive preceding behavioral change before the initiation of therapy, and the ongoing engagement throughout therapy [40]. Theoretically, the concept is most profoundly described as a core component in the “stage of change” dimension of the so-called Transtheoretical Model of behavioral change set forward by Prochaska and DiClemente [41]. In the “stage of change” dimension, patients are assumed to vary in their overall readiness to change, being on different levels ranging from “pre-contemplation” to being ambivalent about change (“contemplation”), having intentions to change (“preparation”), starting changes (“action”), and consolidating changes (“maintenance”).

Studies have consistently found patients’ readiness to change to be an important factor in predicting and moderating their psychotherapy outcomes [42]. Regarding anxiety disorders, research indicates that patients’ readiness to change reduces symptoms and improves other process variables, such as working alliance and adherence to treatment [43]. However, data suggests that up to 80% of patients are not ready for change (to pursue treatment goals) when they enter treatment and possess ambivalence about therapy [44].

We expect that MCA will increase patients’ readiness for psychotherapy, as assessed by the University of Rhode Island’s Change Assessment Scale (URICA) (contemplation subscale) and the Readiness for Psychotherapy Index (RPI), and will increase engagement in psychotherapy as measured by attendance. We expect that more than one mechanism of action is at play: (a) the patient will develop a relationship with the MCA accessor and the outpatient clinic during the course of MCA, which will carry over to the therapeutic relationship with the psychotherapist; (b) due to the structural MCA format, the patient will be confident that her problems are seen and understood; (c) the patient will understand herself, her problems, and personal strengths and will be able to work more effectively on these in therapy; and (d) the therapists will have a greater knowledge of the patient’s problems based on the summaries from the MCA.

### Objectives

The study objectives are to (1) explore the feasibility of MCA as an intervention through rates of recruitment of screened patients, patience’s adherence to MCA or Assessment As Usual (AAU), patient satisfaction ratings, and patient and therapist/clinician evaluations; (2) compare the effect of MCA versus AAU on levels of readiness for psychotherapy in patients referred to group therapy for social phobia or AvPD at end-of-intervention (T1) (main outcome) and after 1-month follow-up (T2); (3) compare the effect of MCA vs AAU on diagnoses (number of diagnostic revisions) and treatment offered (number of patients offered other or additional treatment) in patients referred to group therapy for social phobia or AvPD, as well as adherence to group therapy within the first 4 weeks; and (4) develop a fidelity checklist for the MCA intervention.

We hypothesize that MCA is feasible regarding acceptance and adherence in patients with social phobia or AvPD and is superior to AAU in increasing contemplation score (URICA, see below) at the end of intervention (T1). (2) In addition to this, patients offered MCA have higher service satisfaction ratings (CSQ) than those offered AAU prior to psychotherapy onset, and user evaluation scores of MCA (purpose-made) are positive (more than 3 on a 1–5 Likert Scale).

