## Methods

### Design

The present protocol is based on reporting guidelines from the SPIRIT guideline for Standard Protocol Items for Clinical Trials [45] adapted as recommended when reporting protocols of feasibility trials [46]. The study is designed in order to inform and evaluate the feasibility of a possible future, full-scale RCT of MCA versus AAU. We will evaluate the feasibility of the interventions in terms of clinician resources and patient’s acceptability and adherence to the intervention and comparator, selected based on recommendations for the conduct of feasibility trials [47–49].

In addition to these feasibility outcomes, we will assess outcomes regarding readiness for change, symptoms, and regarding self-esteem and self-efficacy. Data are gathered from patients through a number of questionnaires delivered by the RedCap © webmodule prior to randomization (T0), at the end of MCA (T1) and after 4 weeks of psychotherapy (T2)—the absolute time depends on clinical logistics and timing of group therapy onset.

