#### Outcomes’ objective 2: Trial outcomes

See Table 1 for a table of measurements.

**Table 1 Tab1:** Table of measurements CO-ASSM-RCT

	**Baseline (T0)**	**End of intervention (T1)**	**After 4 sessions of group psychotherapy (T2)**
URICA	x	x	
LSAS	x	x	x
RSES	x	x	x
GSES	x	x	x
CSQ-8 ^a^		x	x
PROM	x	x	x
EHR ^a^			x
EQ ^a^		x	
RPI	x	x	

^a^Feasibility outcomes

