### Primary outcome

#### University of Rhode Island Change Assessment Scale (URICA)

URICA is a 32-item self-report measure including 4 subscales, designed to quantify the patient’s motivation for change: The four subscales are Pre-contemplation, Contemplation, Action, and Maintenance [60]. We will utilize the Contemplation score as our primary outcome.

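### Objective 2 promises an MCA-versus-AAU comparison of readiness at T2, but Table 1 schedules both readiness instruments at T0 and T1 only

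*Protocol article*

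**What the plan says.** In the Objectives section, the second objective is to "compare the effect of MCA versus AAU on levels of readiness for psychotherapy" in patients referred to group therapy, "at end-of-intervention (T1) (main outcome) and after 1-month follow-up (T2"). The same section states the superiority hypothesis for one time point only: MCA "is superior to AAU in increasing contemplation score (URICA, see below) at the end of intervention (T1").

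The section on readiness for psychotherapy says which instruments measure the construct: "URICA) (contemplation subscale) and the Readiness for Psychotherapy Index (RPI"). The primary outcome section adds "We will utilize the Contemplation score as our primary outcome". The RPI is listed as exploratory. No other instrument in the article is described as a measure of readiness.

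Table 1, under the heading for the outcomes of objective 2, marks URICA and RPI at baseline and end of intervention. Neither has a mark in the third column, which is headed "After 4 sessions of group psychotherapy (T2").

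The Design section says questionnaires are gathered "prior to randomization (T0), at the end of MCA (T1) and after 4 weeks of psychotherapy (T2"), without naming which are given at which time.

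**The concern.** A stated between-arm objective needs an outcome measured at the time it names. If Table 1 is followed, no patient in either arm completes a readiness measure at T2, and that part of objective 2 cannot be answered. Analysis cannot repair this. The multiple imputation planned under Statistical considerations needs some observed values of the variable at that visit, and there would be none.

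Two things are at stake. Therapy is given after the primary endpoint, so T2 is the only scheduled contact at which readiness could be seen after therapy has begun. The trial is also meant to supply effect sizes for a later trial, and as scheduled it would supply none for readiness at T2. In addition, if the objective stays as worded, the final report will lack a comparison that the protocol announced, and a reader could take that for selective reporting.

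**Working it through.** No figure in the plan settles this point. The check sets the objective beside the schedule.

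**1. What must be measured.** Objective 2 asks for readiness, by arm, at T1 and T2. The readiness instruments are URICA and RPI.

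**2. What Table 1 schedules.**

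| Instrument | T0 | T1 | T2 |
|---|---|---|---|
| URICA | x | x | – |
| RPI | x | x | – |
| LSAS, RSES, GSES, PROM | x | x | x |
| CSQ-8 | – | x | x |
| EQ | – | x | – |
| EHR | – | – | x |

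Readiness instruments scheduled: 2 of 2 at T0, 2 of 2 at T1, 0 of 2 at T2.

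**3. Is the blank an artefact of text extraction?** Unlikely. Four rows carry three marks, EHR carries a mark at T2 only, and EQ carries one at T1 only. The columns are intact, and both readiness rows show the same pattern.

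**4. Does another section schedule readiness at T2?** No. The Design section gives the three collection times in general terms and names no instrument for T2. The EHR data at T2 are no-shows and diagnostic re-classifications. The readiness section treats attendance as engagement, separately from readiness, and the Objectives place adherence to group therapy under objective 3.

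**5. Does the gap reach the primary comparison?** No. The hypothesis concerns Contemplation at T1, where URICA is scheduled. The sample size also rests on Contemplation: means of 37.3 (SD 1.9) and 34.4 (SD 3.4), 5% significance and 90% power. With a difference of 37.3 − 34.4 = 2.9, a two-sided test and the simple average SD of (1.9 + 3.4)/2 = 2.65:

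n per arm = 2 × (1.960 + 1.282)² × 2.65² / 2.9² ≈ 17.6, rounded up to 18, total 36.

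This is the stated 36. With the root-mean-square SD of 2.754 the same formula gives 19 per arm, total 38. Neither result depends on T2.

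**6. How T2 is defined.** It appears in three forms: a 1-month follow-up (Objectives), 4 weeks of psychotherapy (Design) and 4 sessions of group psychotherapy (Table 1). These need not fall on the same date. The Design section says absolute timing depends on clinical logistics and the start of group therapy, and patients may wait between the end of MCA and the first group session.

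**The case against.** The strongest reply is that little is lost. T1 is labelled the main outcome, no hypothesis is stated for readiness at T2, the trial's primary aim is feasibility, and none of the feasibility criteria uses URICA or RPI. All of this stands. A reader might infer that half of objective 2 is lost or that the main result is at risk. The documents do not support either reading, because they rank T1 above T2.

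A reader might also infer that persistence of readiness into therapy is the reason for the intervention, so that its rationale goes untested. The readiness section does describe mechanisms that carry over into therapy. Its stated expectation, however, is higher readiness together with better engagement measured by attendance. Attendance is covered by objective 3 and by no-shows at T2. Attendance is not readiness, so the gap remains, but carry-over into therapy is not left unmeasured.

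Third, the conflict does not show which place is wrong. Table 1 may have omitted two marks, or objective 2 may be loosely worded: the outcomes listed under its heading include LSAS, RSES, GSES and PROM, which are all measured at T2. It therefore goes too far to say that readiness at T2 is missing by design in all 42 patients. That holds only if Table 1 is correct. Fig. 2 is not available here. It might show which version was intended, but it could not remove the conflict between the text and the table.

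Finally, leaving Contemplation out at T2 can be defended. In the stage model that the article describes, contemplation precedes preparation and action. A lower score after therapy has started could mean progress to action or loss of motivation. This bears on how a T2 result should be read. It does not excuse an objective that has no scheduled data.

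**Conclusion.** The inconsistency is real and of moderate severity. On the schedule as written, the T2 readiness comparison in objective 2 has no data on either readiness instrument. The loss is confined to one subordinate time point without a hypothesis. The T1 primary comparison, its hypothesis and the sample size are unaffected.

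The conclusion assumes that Table 1 is printed as the authors intended and that URICA and RPI are the only readiness measures. If URICA was in fact given at T2, the fault lies in the table and the comparison can be made. Either way, objective 2 and Table 1 cannot both stand.

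**What to change.** First establish whether URICA was given at T2. Then take one of three routes.

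- **T2 collection still open and URICA not yet included:** add URICA to the T2 REDCap questionnaires and to Table 1. Report Contemplation at T2 as a secondary outcome, alongside the Pre-contemplation, Action and Maintenance subscales, so that a fall in Contemplation can be told apart from movement to action. State how many patients per arm had passed T2 before the change.
- **URICA already collected at T2:** correct Table 1.
- **URICA not collected and T2 closed:** remove T2 from objective 2 and state that readiness is compared at T1 only.

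The dates make the first route uncertain. The last inclusion was expected in January 2023, the intervention ran to April 2023, and the article appeared in June 2023. Many T2 contacts may already have passed, although their timing depends on when each group started.

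In the same amendment, settle on one description of T2 and use it in Objectives, Design and Table 1.

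Cost: the first route adds 32 items to a contact that already carries at least 24 + 10 + 10 + 19 = 63 (LSAS, RSES, GSES, PROM), plus the CSQ-8. Adding the RPI as well would mean 42 more, so URICA alone is the lighter choice. The other two routes are short corrections to the text, which can be reported through the channel that the article already names for protocol deviations.
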